### Trial entry

To maximise participation, women will be recruited to this trial by way of both a conventional ‘opt-in’ approach, and a novel ‘opt-out’ strategy implemented following release in March 2014 of the revised National Health and Medical Research Council’s statement on ethical conduct in human research [53], which provided a framework for the use of opt-out consent.

#### Opt-in consent

Using verbal and written approaches, women planning vaginal birth will be informed of the trial during their antenatal visits, focusing specifically on third trimester hospital clinic visits. If an abnormal FHR traces emerges during labour and the woman is able to comprehend the study, she will be approached to participate.

#### Opt-out consent

From August 2014, eligible women booked and receiving antenatal care at the Royal Women’s Hospital will be provided with written information about the trial at various gestations, including the fact that both using and not using lactate measurement are both common strategies at RWH and are accepted as appropriate by senior clinical staff. The women will be advised that, if they subsequently meet the inclusion criteria and none of the exclusion criteria during labour, they will be part of the trial unless they let the clinical or research staff know that they wish to opt-out. They can let the staff know in a number of ways: verbally, by telephone or email. This information is then recorded in the woman’s medical record and in a register, maintained by and accessible to the appropriate clinicians and researchers. Both opt-in and opt-out consenting processes will continue from August 2014.

### Randomisation and group allocation

A researcher not otherwise involved with the trial will use computerised sequence generation with permuted block randomisation, stratified for parity (nulliparous, parous), to develop the randomisation sequence that will be applied through sequentially numbered, sealed, opaque envelopes. Those women whose CTGs meet the inclusion criteria will be randomised in a 1:1 ratio to the CTG-only group or the CTG + lactate group. Clinical care during labour and birth will continue with the woman’s obstetric and midwifery team. Neonatal care will be the provided by the neonatal team, according to national resuscitation guidelines.

#### Both groups

The hospital’s clinical practice guideline for CTG management will be followed for measures to alleviate umbilical cord compression and/or improve placental blood flow to the fetus, such as maternal position change, correction of hypotension or discontinuation of an oxytocin infusion. Umbilical venous and arterial cord blood will be collected at birth for blood gas analysis.

#### CTG-only group

Following identification of an eligible CTG (Table 1) and randomisation to the CTG-only arm, monitoring of fetal well-being will continue. No FBS will be taken, even when a non-reassuring CTG persists despite measures for improving the CTG. Timing of and progress to normal birth, operative vaginal birth or caesarean section, including for the indication of non-reassuring fetal status, will be at the discretion of the clinicians in consultation with the labouring woman.

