### The burden of disease associated with caesarean sections

Despite the evidence that caesarean section rates above 15 % seem to do more harm than good [3], countries such as Australia, the United States of America and China report alarmingly high rates of 27-50 % [1, 4, 5]. The Australian caesarean section rate of 32 % translates to over 95,000 women having this surgery per year, with over 39,000 of these occurring following the onset of labour [4].

Risks that are increased with a caesarean birth include anaesthetic risks, maternal infection, venous thromboembolism, haemorrhage [6, 7] and intensive care unit admissions for babies with breathing difficulties [8]. Having had a caesarean section delivery increases risks in subsequent pregnancies of having further caesarean sections, stillbirth, rupture of the uterus, hysterectomy and increased bleeding due to the placenta implanting over the scar [9–11]. These concerns must be balanced against the need on occasions to urgently deliver a sick baby who would be compromised by remaining in the uterus.

A common indication for caesarean sections following the onset of labour is the identification of a non-reassuring fetal heart rate pattern. The chief investigator of this study has previously found that 38 % of Australian labouring women, where a non-reassuring fetal heart rate pattern had been identified, proceeded to delivery by caesarean section if no further testing of fetal well-being was performed (i.e. for pH or lactate). On the other hand, the caesarean section rate was 10 % when such testing was undertaken [12].

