### Hypothesis

When a woman in labour has a non-reassuring CTG, she has a 38 % chance of delivery by caesarean section [12]. We hypothesise that the addition of FSBLM will reduce this rate from 38 % to 25 %, which is a 35 % relative reduction.

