### Exclusion criteria

Planned caesarean sectionKnown viral infections where FBS is contraindicated (e.g. hepatitis, HIV)Situations requiring immediate delivery, e.g. significant intrapartum haemorrhage, cord prolapse, etc.Known significant fetal anomaly or bleeding disorder

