### Sample size calculations

Data from the systematic review of CTG + FBS trials and observational data from Australian hospitals support a conservative estimate of up to a 40 % relative risk reduction in caesarean sections when FBS is added to CTG monitoring [12, 27, 28]. Based on a conservative 35 % relative reduction in Caesarean Section, from 38 % of women who exhibit a non-reassuring CTG during labour to 25 %, a sample size rounded up to 300 in each group is required (total 600, alpha 0.049 (to allow for one interim analysis), power 90 %). The trial would also have 92 % power to detect a 25 % reduction in combined operative births (caesarean + vacuum + forceps) from 55 % to 41 % [12].

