### Personnel

We are an experienced team with a strong track record in fetal welfare assessment, including the only NHMRC-funded Australian multicentre randomised trial of fetal oximetry, with its related Cochrane systematic review [49–52, 59]. Our team includes authors of the Cochrane systematic review of intrapartum lactate, co-authors of the RWH Clinical Practice Guideline for fetal blood sampling, the Medical and Midwifery Directors of Birth Suite, obstetric care team leaders, an Epidemiologist, and Neonatologists with experience in large, international randomised trials.

The Steering Committee will be chaired by [name] and will comprise the experienced team of named investigators, with relevant experience in midwifery, obstetrics, neonatology, and RCTs. The Data Management Team will comprise the Chief Investigators and Associate Investigators and the Clinical Research Midwives. Clinical Research Midwives will conduct the trial on a day-to-day basis, during office hours. A statistician will be contracted to assist in setting up and maintaining the database, providing data to the data monitoring and safety committee and the interim and final analyses. We will contract a Health Economist to conduct the economic analysis of the trial.

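### Women who already have a scalp lactate or pH result in the current labour are not excluded, so some CTG-only women could be managed on a known result and the contrast diluted

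*Protocol article*

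**What the plan says.** All references are to the Protocol article.

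- **Aim:** the comparison is CTG plus scalp lactate against monitoring by CTG alone.
- **Inclusion criteria and Table 1:** entry depends on an eligible abnormal trace that conservative measures have not improved, plus consent, singleton, gestation, presentation, dilatation and membrane criteria. Earlier scalp sampling is not mentioned.
- **Exclusion criteria:** there are four items: planned caesarean, a viral infection that rules out sampling, a known fetal anomaly or bleeding disorder, and "Situations requiring immediate delivery, e.g. significant intrapartum haemorrhage, cord prolapse, etc". None concerns a sample already taken.
- **Randomisation and group allocation:** women whose traces meet the criteria are randomised 1:1. The trace need not be the first abnormal one.
- **CTG-only group:** after randomisation, "No FBS will be taken, even when a non-reassuring CTG persists despite measures for improving the CTG". Timing and mode of birth are left to the clinicians with the woman.
- **Opt-out consent:** women are told that "both using and not using lactate measurement are both common strategies at RWH and are accepted as appropriate by senior clinical staff".
- **Personnel:** "Clinical Research Midwives will conduct the trial on a day-to-day basis, during office hours".
- **The burden of disease associated with caesarean sections:** the 38% rate belongs to women who "proceeded to delivery by caesarean section if no further testing of fetal well-being was performed (i.e. for pH or lactate").

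**The concern.** The control condition is defined by the absence of scalp testing, but the text secures that absence only from allocation onwards. At a single site where lactate is an accepted routine option, a woman can be sampled as usual care, still have an eligible trace, and then be enrolled. Table 2, which is aligned with the hospital guideline, itself provides for women who remain in labour with a persisting abnormality and a known low result. If such a woman is allocated to CTG-only, her clinicians hold a lactate value and nothing in the plan keeps it out of a discretionary decision about caesarean section.

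Two things are at stake. The control arm would depart from CTG alone as the Aim states it, and from the untested women who supply the planning rate. The difference in caesarean rates would also shrink, at a cost in power.

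**Working it through.** **Inputs.** Sample size calculations: a reduction "from 38 % of women who exhibit a non-reassuring CTG during labour to 25" per cent, 300 per group, alpha 0.049, power 90%. Sidedness is not stated; two-sided is used here, so z = 1.969 for alpha and 1.282 for 90% power.

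**The plan's own figure.** With p1 = 0.38, p2 = 0.25 and mean p = 0.315:

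n = [1.969 × √(2 × 0.315 × 0.685) + 1.282 × √(0.38 × 0.62 + 0.25 × 0.75)]² / 0.13² ≈ 268 per group, or 283 with continuity correction.

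Both agree with a figure described as rounded up to 300. At 300 per group, power is:

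Φ[(0.13 − 1.969 × 0.03793) / 0.03755] = 93.0% (pooled variance under the null).

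The simpler unpooled form, Φ[0.13 / 0.03755 − 1.969], gives 93.2%. With continuity correction it is 91.7%.

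**Dilution.** Let s be the share of CTG-only women with a result before randomisation. The document does not give s, so a range is shown. As an upper-end assumption, give these women the full lactate-arm rate of 25% and all other controls 38%:

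control rate = 0.38 − s × (0.38 − 0.25) = 0.38 − 0.13s.

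The lactate arm stays at 25%, with 300 per group and alpha 0.049.

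| s | Control rate | Difference (points) | Power, pooled | Power, unpooled | n per group for 90% (pooled) |
|---|---|---|---|---|---|
| 0 | 38.0% | 13.0 | 93.0% | 93.2% | 268 |
| 5% | 37.35% | 12.35 | 90.5% | 90.8% | 296 |
| 10% | 36.7% | 11.7 | 87.4% | 87.7% | 328 |
| 20% | 35.4% | 10.4 | 79.1% | 79.5% | 410 |

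**A milder assumption.** If one earlier result delivers half the benefit, those women have a rate of 0.38 − 0.065 = 31.5%, and the control rate is 0.38 − 0.065s. A share of 10% then acts like 5% in the table (37.35%, power about 91%), and 20% acts like 10% (36.7%, power about 87-88%).

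**Reading.** The rounding up to 300 absorbs a share of about 5% even under the upper-end assumption. Power falls clearly below 90% only if the share is 10% or more and an earlier result works nearly as well as the whole lactate strategy.

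**The case against.** The strongest reply is that the trigger for entry is also the trigger for sampling. Table 1 defines a trace eligible for further evaluation by scalp sampling, and both arm descriptions begin with an eligible trace followed by randomisation. The natural reading is that women are randomised at the first eligible trace, before any sample. This stands as far as it goes: the case is probably uncommon. But the text does not require that order, and a woman who is sampled off-trial and enrolled later breaks no stated criterion.

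A reader might also infer more than the documents support:

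- **That overnight sampling followed by morning enrolment is routine.** Office hours describe the research midwives' work. Randomisation is by sealed envelope and is nowhere restricted to those hours. The repeat intervals in Table 2, and its call for urgent delivery above the top threshold, also leave few women undelivered and still eligible many hours later.
- **That such a control has received the experimental strategy.** The intervention is sampling with repeats and action thresholds after allocation. One earlier result is less than that, so the 25% rate is an upper-end assumption.
- **That the observational rate should be used instead.** The background reports that "the caesarean section rate was 10 % when such testing was undertaken". Putting 10% in place of 25% would give power of 86.8%, 77.6% and 51.4% at the three shares. That figure is non-randomised and open to selection, and it lies well below the 25% the trial expects in its own lactate arm.
- **That the comparison is confounded.** Prior sampling precedes randomisation and is balanced by it in expectation. The harm is dilution, not confounding.
- **That the audit cannot separate earlier samples from breaches.** The Compliance section relies on hospital record review, and nothing suggests that sample times are missing. The section simply does not ask for the split.

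**Conclusion.** The gap is real but modest. The eligibility criteria admit women who already have a scalp lactate or pH result in the current labour, and the CTG-only rule does not reach back before randomisation. Any such women in the control arm fall outside the CTG-alone question and the population behind the 38% rate, and they pull the difference towards zero.

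The size cannot be fixed from the document, because the share is not given. With two-sided alpha of 0.049, 300 per group and a 25% rate in these women, power would be about 91%, 88% and 79-80% at shares of 5%, 10% and 20%, against about 93% with none. A smaller effect of a single earlier result, which is more likely, would cost less. The stated sample size itself reproduces and is not in question. This is a cheap improvement.

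**What to change.** Add one line to the Exclusion criteria: *fetal scalp blood lactate or pH result already obtained in the current labour*. Equivalently, state under Randomisation and group allocation that randomisation must precede any scalp sample. The line refers to a result, not an attempt, because a failed attempt gives clinicians no value to act on.

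In the Compliance section, have the audit report sampling before and after randomisation separately in each group, and count only the latter as non-compliance. Earlier samples that slip through then stay visible.

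The cost is a record check at entry and the loss of a few otherwise eligible women. The sample size need not change.

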#### CTG + lactate group

Following identification of an eligible CTG (Table 1) and randomisation to the CTG + lactate arm, if a non-reassuring CTG persists despite measures for improving the CTG, the timing and options for delivery will incorporate a further evaluation of fetal well-being. Fetal blood sampling for lactate measurement will be undertaken, with resulting actions as per Table 2 (developed from the available evidence and aligned with the Clinical Practice Guideline of the RWH [39]).

**Table 2 Tab2:** Clinical management for lactate results in the CTG + lactate group

Lactate (mmol/L)	Action
<4.0 mmol/L	Repeat FBS in 1 hour if the FHR abnormality persists
4.0-4.8 mmol/L	Repeat FBS within 30 minutes or consider expediting the birth if rapid rise since last sample
>4.8 mmol/L	Urgent delivery indicated

### Data collection

Baseline demographic and characteristic data will be abstracted from the participants’ hospital records by the clinical research midwives. In keeping with the requirements of the Consort Statement [48], the Clinical Research Midwives will record the number of women potentially eligible for enrolment in the RCT, the reasons for non-enrolment (e.g. laboured too quickly) and limited data on non-enrolled women that are routinely collected for clinical audit, for example, mode of birth, parity, Apgar scores, to achieve representative enrolment. The primary and clinical secondary outcomes will be abstracted from the participants’ medical records by the Clinical Research Midwives.

#### Women’s experiences

We developed a questionnaire of women’s experiences with labour, monitoring and research specifically for our fetal oximetry trial, drawing on key concepts from experts and peer-reviewed literature [51]. The Cronbach’s alpha (0.83 in each of the study groups) and item-total correlation (*p* < 0.001) supported the reliability and validity of the questionnaire. We will use the nine questions of the ten in the original survey [51] that are relevant to this lactate trial. These questions will seek a rating of “poor”, “fair”, “good” or “excellent” in regard to three domains:(i)labour(ii) monitoring of fetal well-being during labour and(iii) participation in the research.

Provision will also be made for free-text comments. The questionnaire will be administered by the research midwives. It will be returned via the internal hospital mail if completed prior to discharge. If the woman has been discharged without being given a questionnaire, we will contact her by phone or mail to send a questionnaire and postage paid envelope for its return. We will follow women up with one phone call or letter if the questionnaire is not returned.

#### Economic analysis

An economic analysis will be undertaken using cost-effectiveness analysis (CEA) to compare the cost and effectiveness of the experimental clinical strategy: adding lactate estimation to conventional CTG monitoring, versus conventional CTG alone. This method determines the “price” of the additional outcome purchased by changing from one practice (CTG-only) to the alternative strategy (CTG + lactate). The CEA will examine change in resource use for the primary endpoint: caesarean section. Costs for treatment related expenses will include direct medical costs, such as fetal monitoring procedures, equipment, mode of birth and postnatal stay. Given the uniformity of the treatment environment in which the study will be undertaken, we consider a limited perspective of costs from the viewpoint of the health service, in which we already have experience, will be appropriate for this evaluation [52, 54, 55].

### Study endpoints

#### Primary study endpoint: caesarean section

The Cochrane systematic review of lactate measurement in labour identified the caesarean section rate as a key endpoint for the evaluation of this form of fetal welfare assessment [2].

#### Secondary study endpoints

Maternal endpoints, identified in the Cochrane systematic review [2]:Total operative birth (forceps + vacuum + caesarean section)Total operative vaginal birth (forceps + vacuum)Normal vaginal birthCaesarean section specifically for the indication of non-reassuring fetal statusAssisted vaginal birth (forceps or vacuum) for non-reassuring fetal statusMaternal satisfaction with fetal monitoring in labourMaternal length of hospital stayFetal/neonatal endpointsThe fetal oximetry trial [50] demonstrated equivalence in fetal and neonatal outcomes when comparing the use of CTG with fetal oximetry added to CTG. This is relevant, because although poor outcomes resulting from hypoxia are rare, they are important. For this reason, our team of investigators includes experienced neonatologists. Based on recommendations for definitions of serious outcomes by the Australian New Zealand Neonatal Network and expert recommendation for important measures of morbidity at and beyond term [56, 57], we will record:Composite fetal/neonatal endpoint: Death or serious outcome for the infant: includes one or more of fetal death after trial entry; death of a liveborn infant prior to hospital discharge; neonatal encephalopathy (stages II/III) [58]; Apgar score <4 at 5 min; care in neonatal intensive care unit >96 h.Other neonatal morbidity outcomes will include: individual components of the composite fetal/neonatal outcome; neonatal encephalopathy (stages I, II, III) [58]; Apgar score <7 at 5 min; umbilical cord arterial and venous and first neonatal blood gas (within two hours of birth) pH, base deficit and lactate; resuscitation by bag and mask ventilation, intubation, external cardiac massage and/or adrenaline; admission to neonatal intensive care; neonatal length of hospital stay.Economic: Cost-effectiveness of fetal monitoringConsiderations related to fetal scalp blood lactate measurement only: We will also record the success rate of fetal scalp blood sampling for fetal lactate and fetal scalp laceration or infection requiring treatment.

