### Fetal scalp blood sampling

Collection of a small capillary blood sample from the fetal scalp (a fetal blood sample) for blood gas analysis has been used in clinical practice since the 1960s to assist in intrapartum fetal welfare evaluation [21]. Following identification of one abnormal or two non-reassuring features on the CTG, the National Institute for Health and Care Excellence in the United Kingdom recommends fetal blood sampling (FBS) for pH or lactate estimation, with a published action algorithm based on the result [14]. Following rupture of the amniotic membranes and at cervical dilatation greater than or equal to approximately 3 cm, an amnioscope is placed vaginally to allow adequate visualisation of the fetal head. A small sample of blood is then taken from the fetal scalp. This procedure may be uncomfortable and intrusive for the mother and is invasive to the baby. Rare complications include fetal scalp infection and haemorrhage [22, 23] and it is contra-indicated when the mother is known to have HIV or viral hepatitis, or where there is suspicion of a bleeding tendency in the fetus [23, 24].

Traditionally, such testing has required approximately 30 to 50 microlitres of blood, which is often difficult to obtain [25]. Even when the clinician is able to collect this quantity of blood, samples are frequently rejected by the testing equipment due to contamination with air or amniotic fluid. Some equipment can analyse for other components, such as lactate. Fetal lactate testing equipment requiring a much smaller blood volume (as little as 5 microlitres) is now available [26].

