### Compliance

Compliance with the protocol for the trial study groups will be audited by hospital record review of actual attempts to take FBS for lactate estimation in each group. Barriers to compliance will be identified and, where possible, addressed as soon as practical during the trial.

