### Analysis

The consultant statistician for the interim analysis will present data to the data monitoring committee in unlabelled study groups. The data management team will remain blinded to group allocation until the final analysis. Analysis will be by intention to treat and all randomised subjects will be included. Demographic information will be summarised for the groups using descriptive statistics, to ensure the groups are comparable. Proportions will be compared by Chi-squared analysis, risk ratios and their 95 % confidence intervals. Continuous variables will be compared by t-tests or their non-parametric equivalent. Logistic regression will compare the between-group difference in caesarean section. Time to event data will be analysed by Kaplan-Meier statistics. Women’s scores from the maternal perceptions questionnaire will be compared for the two groups using Wilcoxon signed rank test.

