### Independent data monitoring and safety committee (DSMC)

The DMSC (to be convened) will include as a minimum an experienced researcher, a statistician and other personnel with extensive research experience. The Committee will conduct the interim analysis when 50 % of the sample has been recruited and their outcomes are known. A recommendation to stop or modify the trial will be made to the Steering Committee if: (i) it is beyond reasonable doubt that the probability of finding a difference in caesarean section rates between groups is <0.001; or (ii) serious adverse events are worse in one group than another.

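### Treated fetal scalp laceration or infection is listed only as a lactate-sampling item, so this harm has no planned control-arm count

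*Protocol article*

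**What the plan says.** Secondary study endpoints gives a composite infant outcome ("Composite fetal/neonatal endpoint: Death or serious outcome for the infant") and a list of other neonatal morbidity. Neither is limited to one arm. After an economic item comes a lead-in that confines what follows to considerations of lactate measurement alone, and under it: "We will also record the success rate of fetal scalp blood sampling for fetal lactate and fetal scalp laceration or infection requiring treatment". Scalp injury is in neither the composite nor the other morbidity list.

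Other sections bear on the point:

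- Fetal scalp blood sampling describes the procedure as invasive to the baby and says: "Rare complications include fetal scalp infection and haemorrhage". It gives no rate.
- CTG-only group rules out sampling in controls: "No FBS will be taken, even when a non-reassuring CTG persists despite measures for improving the CTG".
- Compliance audits "actual attempts to take FBS for lactate estimation in each group".
- Analysis states: "Analysis will be by intention to treat and all randomised subjects will be included".
- The DSMC section lets the committee recommend stopping or changing the trial if "serious adverse events are worse in one group than another".

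**The concern.** The two items under the lactate-only lead-in differ in kind. Sampling success is undefined without an attempt at sampling, so a one-arm measure is right for it. Scalp laceration or infection is a state of the infant, and it can be looked for in every infant whatever the allocation.

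The article argues that the trial is needed because randomised evidence on both the benefits and the risks of lactate sampling is lacking (section on the need for a randomised trial). A count in one arm describes what was seen there. It does not estimate what sampling added, because nothing shows how many such injuries would have occurred without it. At stake is whether the trial can report the excess of a complication that it attributes to its own intervention. The trial is unblinded, so deciding case by case which injuries sampling caused would fall to people who know the allocation. A comparison by arm does not need that judgement.

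**Working it through.** No figure in the article is in dispute, so the main check is a reading of the sections side by side.

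**1. Where the outcome is listed.** Composite infant outcome: no scalp item. Other neonatal morbidity: no scalp item. Lactate-only item: sampling success and scalp laceration or infection. The plain reading is that no control-arm count is planned.

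**2. Whether another section supplies one.**
- Data collection says that research midwives take the clinical secondary outcomes from participants' records. It names no arm, but it also does not widen an outcome that the endpoint list has narrowed.
- Analysis includes all randomised subjects, but that governs how recorded data are analysed, not what is recorded.
- The DSMC rule covers serious adverse events. The scalp outcome is defined by needing treatment, which is a lower threshold.

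None of the three provides a stated control-arm record of treated, non-serious scalp injury.

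**3. Whether other causes can operate in both arms.** Forceps and vacuum births are outcomes in both groups. Sample size calculations plans on 38% versus 25% caesarean births and 55% versus 41% operative births of all kinds. By subtraction, operative vaginal birth is:
- CTG-only: 55% − 38% = 17%, or 0.17 × 300 = 51 women
- CTG + lactate: 41% − 25% = 16%, or 0.16 × 300 = 48 women

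The article does not say that instrumental birth injures the scalp. That is my premise, taken as general clinical knowledge and without a rate.

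**4. What a one-arm count estimates.** Let *b* be the risk of treated scalp injury from causes other than sampling and *s* the risk that sampling adds. The lactate arm alone estimates *b* + *s*, and the control arm estimates *b*. Only the difference gives *s*. With no control count and no attribution rule, *s* cannot be recovered.

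**5. Illustration on assumed risks.** The article gives neither *b* nor *s*. I assume *b* from 0.5% to 3% and *s* from 0.5% to 2%, only to show how the problem behaves. The share of lactate-arm injuries not due to sampling is *b*/(*b* + *s*):
- lowest: 0.5/(0.5 + 2) = 20%
- highest: 3/(3 + 0.5) = 86%

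**6. What a two-arm comparison would give.** On the same assumptions, with 300 per arm, two-sided alpha 0.05 and the normal approximation, power runs from about 5% (*b* = 3%, *s* = 0.5%) to about 52% (*b* = 0.5%, *s* = 2%). The approximation is rough at such low risks. As an example of precision, take *b* = 1% and *s* = 1%:
- standard error of the difference = √[(0.01 × 0.99 + 0.02 × 0.98)/300] = √(0.0295/300) = 0.0099
- 95% half-width = 1.96 × 0.0099 = 1.9 percentage points, around a difference of 1 point

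The gain is therefore an unbiased estimate, not a powered test.

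**The case against.** The strongest reply is that the lead-in may name a topic rather than an arm: items that arise because sampling exists. Nothing says in terms that control infants go unrecorded. The article condenses a fuller protocol, and a data form not shown may cover both arms. This is fair, and it means that the restrictive reading is the plain one but not the only possible one. It does not dispose of the point, because the outcome is missing from the unrestricted lists and no other section restores it.

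A second reply is that reporting a procedure's complications among those who undergo it is common practice, and that a comparison of rare events would have little power. Both are true. The first does not yield an estimate of excess risk. The second limits what the comparison can show, but does not make a one-arm count more informative.

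Three stronger readings are tempting, and the document does not support them:

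- **That this is the main harm of the intervention.** The article calls the complications rare. Its serious infant outcomes, which carry no arm restriction, are death, encephalopathy, very low Apgar score and prolonged intensive care.
- **That injuries from other causes would be charged to the lactate arm.** The article states no attribution rule. Staff might record only injuries at the sampling site, in which case injuries from instrumental birth would be left out of the count.
- **That a particular number of events would be misattributed.** No background rate is given. The planning figures also put instrumental births nearly level (17% and 16%), so they give no reason to expect a large difference between arms from that source.

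Serious scalp injuries could still reach the committee's between-group review of adverse events.

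**Conclusion.** The point holds in a limited form. On the plain reading of Secondary study endpoints, treated scalp laceration or infection is tied to lactate sampling and has no planned control-arm count. Injury due to sampling cannot then be separated from injury with other causes. The conclusion rests on reading the lead-in as a restriction, and on the premise that scalp injury can also arise without sampling.

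Its size cannot be given in events, because the article contains no rate. The percentages in the illustration depend wholly on assumed risks and are not forecasts. The primary endpoint, its sample size and the serious infant outcomes are untouched. The change should still be made, because it concerns the risk side of a trial that is justified by the lack of randomised evidence on risks.

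**What to change.** Move scalp laceration or infection that needs treatment into the other neonatal morbidity outcomes. Record it for every randomised infant, using one definition that does not depend on the presumed cause. Report it by allocated group under the intention-to-treat rule in the Analysis section, as a risk difference or risk ratio with its 95% confidence interval, and describe it as an estimate rather than a powered test. Leave only the sampling success rate under the lactate-only item. If the full protocol or data form already records the outcome in both arms, one sentence saying so is enough.

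The cost is about one more field in a record review already carried out for participants in both groups. The drawback is an imprecise estimate, because the event is expected to be rare.
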